### Unauthorised treatments

Serotherapy for the current COVID-19 episode will not be permitted.

Patients with prior anti-COVID-19 vaccine are not excluded whatever the delay.

Anti-COVID-19 vaccine is not permitted in the study, it is recommended to wait 90 days after the acute covid-19 episode, before proposing an anti-COVID-19 vaccination so as not to risk reducing the immunogenicity of the vaccine.

# Study population

The population to be studied is adults (male or female), over 18 years old, hospitalized for moderate COVID-19 as confirmed by a positive RT-PCR. The patients will be recruited in the investigational sites declared on this study.

Women of childbearing potential (WOCBP) must use appropriate method(s) of contraception during the clinical trial (oral contraception, implant or IUD).

Pregnant woman or Women of childbearing potential (WOCBP) without effective contraception or nursing, patient under guardianship or trusteeship will not be included in the study.

The subjects cannot participate simultaneously in another interventional study and until 3 months after the end of their participation to this study.

## Description of the population in Phase 2a

In the phase 2a, two sequential groups:

- Dose 1 XAV-19 with 0.5 mg/kg (n=6) versus Placebo (n=2)

8 patients receiving two doses of treatment (day 1, day 5) and follow-up until D29

- Dose 2 XAV-19 with 2 mg/kg (n=6) versus Placebo (n=2)

2 first patients receiving two doses of treatment (day 1, day 5) and 6 patients receiving one dose of treatment at 2mg/kg at D1 and all have follow-up until D29

16 patients will be included.

If a patient does not receive the appropriate treatment or has not been followed for 8 days then he will be replaced within the limit of 20 patients in total.

Patients will be treated once or twice in 1 week with XAV-19 (at day 1 and day 5 or only at day 1) and monitored regularly during the study period (see flow chart). Patients will be hospitalized at least from Day 1 to Day 3, if discharged before Day 5 the patient will come back for on-site visits at Day 5, Day 8, Day 15 and Day 29. Visits on Day 4, Day 6, Day 7, Day 11 and Day 13 will be done via phone calls to evaluate the clinical status, collect any adverse event and any new concomitant medications.

### Inclusion criteria

1. Willing and able to provide written informed consent prior to performing study procedures
2. Male or female ≥ 18 years and ≤ 85 years
3. Hospitalized for COVID-19
4. Positive SARS-CoV-2 RT-PCR in any body specimen (nasopharynx, saliva, sputum) ≤ 10 days before enrolment
5. Evidence of pulmonary involvement (on lung examination [rales/crackles] and/or chest-imaging [Chest X-ray or computed tomography])
6. Requiring O2 supplement ≤ 6L/min at screening
7. Requiring O2 supplementation with SpO2 ≥ 92% on O2 therapy at screening
8. First onset of COVID-19 symptoms ≤ 10 days, among fever and/or chills, headache, myalgias, cough, shortness of breath, whichever as occurred fist
9. WOCBP must have a negative urinary pregnancy test the day of inclusion
10. All sexually active male subjects must agree to use an adequate method of contraception throughout the study period and for 90 days after the last dose of study drug and agree to no sperm donation until the end of the study, or for 90 days after the last dose of XAV-19, whichever is longer
11. Patients with French social security

### Exclusion criteria

1. Evidence of multiorgan failure (severe COVID-19)
2. Mechanically ventilated (including ECMO)
3. Receipt of immunoglobulins or any blood products in the past 30 days
4. Psychiatric or cognitive illness or recreational drug/alcohol use that in the opinion of the investigator, would affect subject safety and/or compliance
5. End-stage renal disease (eGFR < 15 ml/min/1,73 m^2^)
6. Child-Pugh C stage liver cirrhosis
7. Decompensated cardiac insufficiency
8. **History of active drug abuse**
9. Known allergy, hypersensitivity, or intolerance to the study drug, or to any of its components
10. Females of childbearing potential without contraceptive method, or with positive pregnancy test, breastfeeding, or planning to become pregnant during the study period
11. Current documented and uncontrolled bacterial infection.
12. Prior severe (grade 3) allergic reactions to plasma transfusion
13. Patient participating in another interventional clinical trial
14. Life expectancy estimated to be less than 6 months
15. Patient under guardianship or trusteeship

## Description of the population in Phase 2b

In the phase 2b, about 398 patients, 199 patients in each group, will be included in this study.

Patients will be treated once with XAV-19 (at day 1) and monitored regularly during the study period (see flow chart). Patients will be hospitalized at least from Day 1 to Day 3, if discharged before Day 5 the patient will come back for on-site visits Day 8, Day 15, except if patient is participating to the ancillary study, in which case he will have to come back on site for the Day 5 and Day 29 visits.

In the terminal ancillary study, 20 patients will be included with the same inclusion and exclusion criteria as the other phase 2b patients. Patients will be treated once with XAV-19 (at day 1) at flat dose and monitored regularly during the study period (see flow chart). Patients will be hospitalized at least from Day 1 to Day 3, if discharged before Day 5 the patient will come back for on-site visits Day 5, 8, 15 and 29.

### Inclusion criteria

1. Willing and able to provide written informed consent prior to performing study procedures
2. Male or female ≥ 18 years
3. Hospitalized for COVID-19
4. Documentation of SARS-Cov-2 infection before enrolment, by positive SARS-CoV-2 RT-PCR or antigen in any body specimen (nasopharynx, oropharynx, saliva, sputum, bronchoalveolar lavage …) before enrolment
5. Evidence of pulmonary involvement (on lung examination [rales/crackles] and/or chest-imaging [Chest X-ray or computed tomography])
6. Requiring O2 supplement ≤ 6L/min at screening
7. Requiring O2 supplementation with SpO2 ≥ 92% on O2 therapy at screening (or ≥ 90 % if chronic obstructive pulmonary disease)
8. First onset of COVID-19 symptoms ≤ 14 days, among fever and/or chills, headache, myalgias, cough, shortness of breath, whichever as occurred fist (other symptoms such as asthenia not to be considered in this list)
9. WOCBP must have a negative urinary pregnancy test the day of inclusion
10. All sexually active male subjects must agree to use an adequate method of contraception throughout the study period and for 90 days after the last dose of study drug and agree to no sperm donation until the end of the study, or for 90 days after the last dose of XAV-19, whichever is longer
11. Patients with French social security

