### Primary endpoint

Patients who died or develop respiratory failure, as defined by the requirement of noninvasive ventilation, high-flow oxygen devices, invasive mechanical ventilation (corresponding to a score of 5 or more on the WHO 8 point ordinal scale) or by an increase of the required O2 supplement more or equals to 10 L/minutes with a non-rebreather mask (oxygen mask with reservoir bag).

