### Exclusion criteria

1. Evidence of multiorgan failure (severe COVID-19)
2. Mechanically ventilated (including ECMO)
3. Receipt of immunoglobulins or any blood products in the past 30 days
4. Psychiatric or cognitive illness or recreational drug/alcohol use that in the opinion of the investigator, would affect subject safety and/or compliance
5. End-stage renal disease (eGFR < 15 ml/min/1,73 m^2^)
6. Child-Pugh C stage liver cirrhosis
7. Decompensated cardiac insufficiency
8. Known allergy, hypersensitivity, or intolerance to the study drug, or to any of its components
9. Females of childbearing potential without contraceptive method, or with positive pregnancy test, breastfeeding, or planning to become pregnant during the study period
10. Current documented and uncontrolled bacterial infection.
11. Prior severe (grade 3) allergic reactions to plasma transfusion
12. Patient participating in another interventional clinical trial
13. Life expectancy estimated to be less than 6 months
14. Patient under guardianship or trusteeship
15. Patient already included
16. Prior hospitalisation in intensive care unit for the current covid-19 episode

Patients with prior anti-COVID-19 vaccine are not excluded whatever the delay.

Anti-COVID-19 vaccine is not permitted in the study, it is recommended to wait 90 days after the acute covid-19 episode, before proposing an anti-COVID-19 vaccination so as not to risk reducing the immunogenicity of the vaccine.

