### Screening Visit (Day –2 / Day 1)

Subjects will be screened within 2 days before randomization and dosing to determine eligibility for participation in the study. The same applies to the terminal ancillary study. Practically, Day 1 is the day following Day-1, so patients can be randomized either one or two days after, or the same day as screening. Following presentation of the study and the informed consent form by the investigator research team, participants will have enough time to take their decision regarding their participation.

- Obtain written informed consent. This should be documented in the medical file of the patient. After the informed consent, the following assessments are performed to determine eligibility requirements as specified in the inclusion and exclusion criteria:
- Focused medical history including the following information (eg, date of first symptoms, overall symptoms, exposure source, demographics, baseline characteristics, allergies and medical history)
- Review and record medications and therapies for this current illness
- Counsel subjects to use adequate birth control methods required during the trial to avoid pregnancy
- Targeted physical examination including, vital signs (heart rate, temperature, blood pressure, level of consciousness), body weight, and height
- Documentation of respiratory status: respiratory rate, oxygen supplementation, SpO2 at rest or PaO2, radiographic findings
- Obtain blood samples if not done in the preceding 48 hours for white blood cell count, hematocrit, platelets, creatinine and creatinine clearance, glucose, total bilirubin, ALT, AST
- Urinary Pregnancy test (for women of childbearing potential)
- Administration of the 8-point Ordinal scale
- Record any serious adverse events and all adverse events related to protocol-mandated procedures occurring after signing of the consent form.

Study subjects who qualify should be immediately randomized, which could occur on same day as screening (Day 1). Randomization and dosing should occur on the same day if possible.

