## Protocol deviations

The following protocol deviations are pre-defined as major protocol violations with a direct bearing on primary outcome:

- Patients who did not respect treatment scheduled (i.e. for who treatment was not administrated or not entirely administrated)

- Patients who did not received the allocated treatment (treatment cross-over)

- Patients who did not verify all major inclusion criteria and all major non-inclusion criteria

- Patients lost to follow-up before day 15

- Patients who withdrew their consent before day 15

- Patients who had a respiratory failure before treatment administration

Protocol deviations will be identified and classified as major or minor in blind reviews before the database freezing. The number and % of patients with major and minor protocol deviations will be provided by treatment group, with details of the type of deviation. No formal statistical comparison will be done.

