**Figure 1. Flow of participation in the POLYCOR trial.**

Screened patients (**n=**)

Excluded (**n=**)

Withdraw consent before randomisation (n=) *

Degradation / improvement of clinical status (n=)

Other reasons (n=)*

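### Phase 2b oxygen limits apply only at screening, so a patient who worsens outside intensive care before randomisation can enter the trial already meeting the primary endpoint

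*Combined protocol and SAP*

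**What the plan says.** **Entry.** Protocol 5.2.1 (repeated in SAP 2.2) sets criterion 6 as "Requiring O2 supplement ≤ 6L/min at screening" and criterion 7 as "Requiring O2 supplementation with SpO2 ≥ 92% on O2 therapy at screening", with a lower saturation limit for COPD. Protocol 6.2.1 states the window: "Subjects will be screened within 2 days before randomization and dosing to determine eligibility for participation in the study". It also asks that qualifying patients be randomised at once, possibly on the day of screening. Protocol 6.2.2 requires eligibility to be confirmed before randomisation on Day 1, and respiratory status and the ordinal score to be recorded before infusion. It sets no Day 1 limit on oxygen flow or device.

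**Exclusions.** In Protocol 5.2.2, exclusion 2 covers mechanical ventilation including ECMO. Exclusion 16 is "Prior hospitalisation in intensive care unit for the current covid-19 episode".

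**Endpoint.** The Phase 2b primary endpoint in the protocol counts death or respiratory failure, "as defined by the requirement of noninvasive ventilation, high-flow oxygen devices, invasive mechanical ventilation", or a non-rebreather mask at 10 L/min or more. SAP 1.3 and the respiratory-failure definition in SAP 5.1 list the same states. SAP 5.1 counts patients with at least one failure after baseline and does not require the failure to be new.

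**Handling in the SAP.** SAP 3.2 lists as a major deviation "Patients who had a respiratory failure before treatment administration". The flow chart (SAP Figure 1) has a line, before randomisation, for patients excluded because their clinical status worsened or improved. SAP 3.3 keeps everyone in ITT, removes untreated patients from mITT (including those left untreated because of rapid respiratory worsening), and removes major deviations from PP.

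**The concern.** The trial asks whether XAV-19 prevents progression to respiratory failure. A patient already on high-flow oxygen or a high-flow reservoir mask when randomised cannot show prevention. That patient adds an event to whichever arm he or she joins. Such events arise equally in both arms in expectation, so they shrink the observed difference. They also put events at the very start of the time-to-respiratory-failure and time-to-NIV/high-flow analyses.

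The SAP foresees these patients but gives no entry threshold. Failure before treatment is a deviation although no oxygen or device criterion at randomisation forbids it, and the flow chart counts exclusions for worsening without saying how much worsening excludes. One site may hold such patients back on judgement while another enrols them under the written criteria.

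**Working it through.** **1. Can such a patient pass the written criteria?** Take a patient on 5 L/min at screening who, on the ward the next morning, needs a reservoir mask at 10 L/min.

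- Criteria 6 and 7: met, because they refer to screening.
- Exclusion 2: not triggered. The documents list NIV and high-flow oxygen separately from invasive ventilation, and a mask is neither.
- Exclusion 16: not triggered, because there was no intensive care stay.
- Day 1 confirmation: passed, because it adds no limit of its own.
- Endpoint: already in a qualifying state.

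At screening itself the 6 L/min cap rules out the 10 L/min mask, so the main route is deterioration in the gap.

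**2. Which analyses include this patient?** ITT: yes. mITT: yes if infused, no if left untreated. PP: no.

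**3. Reproduce the planned size.** Inputs from Protocol 7.2.2 and SAP 2.7: 20% versus 10%, two-sided 5%, 80% power. Using the pooled-variance formula without continuity correction, with mean rate 0.15:

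n = [1.960·√(2·0.15·0.85) + 0.8416·√(0.20·0.80 + 0.10·0.90)]² / 0.10² = (0.9897 + 0.4208)² / 0.01 = 198.96, so 199 per arm and 398 in total. Power at 199 per arm is 80.0%. The figure reproduces and leaves no reserve.

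**4. Add a share f already in failure.** f is an assumption; the documents give none. Suppose these patients count as events in both arms and 20%/10% holds among the rest. The observed rates are then p_C = f + (1−f)·0.20 and p_T = f + (1−f)·0.10. With mean p̄,

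power = Φ{ [√199·(p_C − p_T) − 1.960·√(2p̄(1−p̄))] / √(p_C(1−p_C) + p_T(1−p_T)) }.

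For f = 2%: (1.3825 − 1.0338)/0.5229 = 0.667, and Φ = 0.7475.

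| f | Placebo | XAV-19 | Power at 199 per arm | Total N for 80% |
|---|---|---|---|---|
| 0 | 20.0% | 10.0% | 80.0% | 398 |
| 1% | 20.8% | 10.9% | 77.4% | 426 |
| 2% | 21.6% | 11.8% | 74.8% | 454 |
| 3% | 22.4% | 12.7% | 72.2% | 482 |

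**5. What range of f is plausible?** If 20% failure by Day 15 accrues at a constant rate, the daily hazard is −ln(0.80)/15 = 0.0149. That gives 1 − e^(−0.0149) = 1.5% over one day and 1 − e^(−0.0298) = 2.9% over two. The corresponding power is about 76% and 72%. The two-day figure supposes that every patient waits two days and that everyone who worsens is randomised anyway. It also includes deaths and invasive ventilation, which could not enter.

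**6. Sensitivity to the 20%.** If the 20% control rate already includes baseline cases and treatment halves only the remaining risk, the treated rate is f + (0.20 − f)/2, that is 10.5%, 11.0% or 11.5% for f = 1%, 2% or 3%. Power is then 75.2%, 70.0% or 64.4%. The documents do not say which reading of the 20% applies.

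**The case against.** The case for leaving the text alone has real substance.

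- **Exclusion 16 closes part of the gap.** It carries no screening time limit, and the documents associate high-flow oxygen and NIV with intensive care (Protocol 8.2.1 and the Phase 2a secondary endpoints). A patient moved to intensive care for high-flow oxygen is barred. This stands, so the gap is confined to support given outside intensive care.
- **The gap is often short.** Protocol 6.2.1 asks for immediate randomisation, and for randomisation and dosing on the same day if possible. This also stands, and it lowers f. It does not set a limit for patients who do wait.
- **mITT removes some cases.** It drops patients left untreated because of rapid worsening. Those infused anyway remain.
- **The endpoint says patients develop failure.** That wording suggests a new event, but the SAP 5.1 counting rule does not enforce it.

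A reader might go further and infer that patients on chronic home ventilation are a second route needing their own exclusion. The documents mention neither home ventilation nor CPAP, and how a long-standing device counts is a question about the endpoint definition. A reader might also take f = 5% (power about 67%) as the likely loss. Nothing in the plan supports a share that high: its own 20% by Day 15 implies about 3% at most under a constant rate, although an early-peaking hazard would raise that.

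**Conclusion.** The point holds as a gap in the entry criteria. A patient who deteriorates outside intensive care between screening and randomisation can be randomised while already in a primary-endpoint state, and if infused counts as a failure in ITT and mITT unless that support has ended.

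Under the main assumption (20% versus 10% among all other patients), power falls from 80.0% to between 77.4% and 72.2% for f of 1% to 3%. The upper end corresponds roughly to a constant failure rate over a full two-day gap. The size depends on f, which the documents do not give, and on whether the planned 20% already includes such cases.

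It would be wrong to infer a biased comparison or an inflated type I error: randomisation balances these patients in expectation, and the sample size is correct for its stated inputs. Moderate importance, and a cheap improvement.

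**What to change.** 1. In criteria 6 and 7, replace the reference to screening with *at screening and at randomisation (before the randomisation step)*.
2. Add an exclusion: *already meeting a primary-endpoint respiratory-failure state (NIV, high-flow oxygen, reservoir mask ≥ 10 L/min, invasive ventilation/ECMO) at randomisation*.
3. Repeat both in SAP 2.2, and align the deviation list (SAP 3.2), the flow-chart line (SAP Figure 1) and the counting rule (SAP 5.1) with them.

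No separate exclusion for chronic home ventilation is needed.

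**Cost.** Amendment wording, matching eligibility items in the eCRF, and a few more screen failures. Respiratory status and the ordinal score are already recorded on Day 1 before infusion, so they need only be checked before the randomisation step.

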### Exclusion criteria

1. Evidence of multiorgan failure (severe COVID-19)
2. Mechanically ventilated (including ECMO)
3. Receipt of immunoglobulins or any blood products in the past 30 days
4. Psychiatric or cognitive illness or recreational drug/alcohol use that in the opinion of the investigator, would affect subject safety and/or compliance
5. End-stage renal disease (eGFR < 15 ml/min/1,73 m^2^)
6. Child-Pugh C stage liver cirrhosis
7. Decompensated cardiac insufficiency
8. Known allergy, hypersensitivity, or intolerance to the study drug, or to any of its components
9. Females of childbearing potential without contraceptive method, or with positive pregnancy test, breastfeeding, or planning to become pregnant during the study period
10. Current documented and uncontrolled bacterial infection.
11. Prior severe (grade 3) allergic reactions to plasma transfusion
12. Patient participating in another interventional clinical trial
13. Life expectancy estimated to be less than 6 months
14. Patient under guardianship or trusteeship
15. Patient already included
16. Prior hospitalisation in intensive care unit for the current covid-19 episode

Patients with prior anti-COVID-19 vaccine are not excluded whatever the delay.

Anti-COVID-19 vaccine is not permitted in the study, it is recommended to wait 90 days after the acute covid-19 episode, before proposing an anti-COVID-19 vaccination so as not to risk reducing the immunogenicity of the vaccine.

# Study design and conduct

## Study schedule for phase 2A

The study schedule is summarized in the flowchart below; all of these examinations apply to all patients from phase 2a, the blood collections apply for all patients.

### Screening Visit (Day –2 / Day 1)

Subjects will be screened within 2 days before randomization and dosing to determine eligibility for participation in the study. Following presentation of the study and the informed consent form by the investigator research team, participants will have enough time to take their decision regarding their participation.

- Obtain written informed consent. This should be documented in the medical file of the patient. After the informed consent, the following assessments are performed to determine eligibility requirements as specified in the inclusion and exclusion criteria:
- Focused medical history including the following information (eg, date of first symptoms, overall symptoms, exposure source, demographics, baseline characteristics, allergies and medical history)
- Review and record medications and therapies for this current illness
- Counsel subjects to use adequate birth control methods required during the trial to avoid pregnancy
- Targeted physical examination including, vital signs (heart rate, temperature, blood pressure, level of consciousness), body weight, and height
- Documentation of respiratory status: respiratory rate, oxygen supplementation, SpO2 at rest or PaO2, radiographic findings
- Obtain blood samples if not done in the preceding 48 hours for white blood cell count, hematocrit, platelets, creatinine and creatinine clearance, glucose, total bilirubin, ALT, AST
- Urinary Pregnancy test (for women of childbearing potential)
- Administration of the 7-point Ordinal scale
- Record any serious adverse events and all adverse events related to protocol-mandated procedures occurring after signing of the consent form.

Study subjects who qualify should be immediately randomized, which could occur on same day as screening (Day 1). Randomization and dosing should occur on the same day if possible.

